### Hypotheses

We hypothesize that the PIPA model of care will be at least 15% more clinically effective, and will be more economically efficient and acceptable, than ‘care as usual’. Secondly, we expect that each of the screening measures will have acceptable psychometric characteristics when used in this population of pregnant women.

### Design

This is a comparative-effectiveness study which will compare ‘care as usual’ (the SAFE START model) to an alternative model (the PIPA model) sequentially over a 36 month period (see Fig. 2). It will employ a mixed methods design. The primary aims will be evaluated using a between-groups design, comparing the two models of care on a range of outcomes. The secondary aims will be evaluated using a within group design.

**Fig. 2 Fig2:**
[figure not shown]
Flow chart for the PIPA Project. ^1^ No data collection in Study Year 2 due to state-level upgrade of administrative data platform at the participating site; Training in the PIPA model will take place in the final month of Year 2; ^2^ Time 1 = approx. 12–16 weeks’ gestation; ^3^ Time 2:=2 weeks post-Time 1; ^4^ Excluded from Time 2 if: declined study Expression of Interest (EoI); EoI not asked at booking-in visit; declined participation when contacted at time of Time 2; did not meet inclusion criteria at Time 2; not contacted at Time 2 due to staffing/resource limitations; ^5^ Completed by women in Group 2 only; ^6^ To examine healthcare provider perspectives, survey, observational and key informant interview data will be collected during the final 6 months of the allocation periods for Group 1 and Group 2. Focus groups will be held approx. 3-months after the implementation of the PIPA model of care

### Psychosocial assessment models of care

A summary of the key features of the SAFE START and PIPA models of care are presented in Table 1.

#### SAFE START model (care as usual)

This model of care recommends that all women complete the EPDS and SAFE START psychosocial questions at the initial antenatal booking-in appointment [13]. A paper-based version of the EPDS is completed by the woman and the total score and score on question 10 are manually scored by the midwife and recorded on a state-wide administrative database (ObstetriX; to be superseded by eMaternity), whereas the psychosocial questions are administered face-face by the midwife and responses electronically recorded in the database. The psychosocial questions cover seven key domains of risk: (1) (lack of) social supports; (2) recent stressors in the previous 12 months; (3) anxious personality style or low self-esteem; (4) history of mental health problems; (5) history of childhood abuse; (6) contact with child protective services or having a child living in the care of another person; and (7) current or recent domestic violence. Based on responses to these questions and the EPDS, women fall into one of three SAFE START psychosocial risk levels: Level 1 (no specific vulnerabilities or risk); Level 2 (endorsing one or more of a broad range of risk factors of variable severity and significance) or Level 3 (endorsing one or more complex risk factors, where ‘complex’ risk implies a high degree of psychosocial morbidity associated with greater risk of mental health disorder, lack of engagement with services and risk of poor parenting and infant outcomes, including risk of harm to the infant).

#### Perinatal Integrated Psychosocial Assessment (PIPA) model

The PIPA model of care comprises three key electronic elements:Administration of the Antenatal Risk Questionnaire-Revised (ANRQ-R) questionnaire (covering a range of known psychosocial risk factors) and the EPDS (including four additional questions to aid more guided exploration of recent thoughts of self-harm, among women who endorse EPDS question 10) by the midwife, with responses recorded in eMaternity;A computer-based clinician decision-support algorithm, which generates the woman’s psychosocial risk profile and self-harm risk scores (based on the ANRQ-R and EPDS), summarises the presence/combinations of identified risk factors and articulates six psychosocial risk levels, ranging from No Risk to High Risk;Immediate referral prompts for the midwife conducting the assessment. These clinician prompts are embedded within eMaternity, and are tailored to the woman’s psychosocial risk profile and the on-site services available.

The ANRQ-R is a revised version of the validated ANRQ [24], incorporating the following psychosocial risk domains: possible mental health history (identifying *significant* episodes in terms of impact on function and/or seeking treatment); history of physical, sexual or emotional abuse; current/recent intimate partner violence; level of practical supports; quality of relationship with mother (in childhood) and current partner (if partnered); anxious or perfectionistic personality style; current or recent substance use; and significant levels of stress in the last 12 months as well as questions relating to (homelessness or housing instability, single or teen parenthood, contact with child protection services). The ANRQ-R adheres to the recommendations of the SAFE START model, in terms of the core set of psychosocial variables that are assessed [14].

#### Key differences between the SAFE START and PIPA models of care

While the two psychosocial assessments are similar in content, PIPA differs from the SAFE START in a number of ways. The PIPA model: 1) considers in full all possible psychosocial risk factors identified across the booking visit and provides a *cumulative* measure of their impact by generating a total score on the ANRQ-R; 2) measures the *severity* of a number of risk factors (whereas SAFE START identifies only the presence or absence of these risk factors); 3) *auto-scores* the questionnaires, eliminating manual scoring errors arising in this context [25]; 4) includes additional structured questions to explore self-harm on the EPDS; 5) enables the midwife to document clinical concerns not elicited by the questionnaires, (e.g., the woman’s presentation at interview). This ‘Clinician Concerns’ option duly recognizes the importance of clinicians’ judgment and provides an avenue to refer a woman to the mental health midwife *even if* no risk is identified on the structured questionnaires.

### Setting

The site for the PIPA Project is the Royal Hospital for Women (RHW), a large teaching hospital in metropolitan Sydney, Australia, with approximately 4000 births per year [26].

During the first 12 months of the PIPA Project, women who attend the participating site for their first midwife-led routine antenatal visit will receive care as usual (SAFE START model), while women who attend for their antenatal booking-in visit in the last 12 months of the study will receive the alternative PIPA model of care. There will be an interval of approximately 12 months to allow for the implementation of a new state-wide administrative database (eMaternity), which will incorporate the PIPA model and one month of staff training for the PIPA model. During this time, women attending the hospital will continue to receive care as usual, though no study data will be collected (see Fig. 2).

### Time points for data collection

As shown in Fig. 2, data collected at two time points (Time 1 and Time 2) will inform the assessment of clinical- and cost-effectiveness outcomes, as well as women’s perceptions of the acceptability and perceived benefit of each model of care (Primary Aims). Data collected at these time points will also be used to examine the psychometric properties of a range of screening tools when used in pregnancy (Secondary Aim). Time 1 will be the initial psychosocial assessment (generally conducted at the first antenatal booking-in visit; approx.12 – 16 weeks gestation) and Time 2 will be approximately 2 weeks post-Time 1.

A range of data collection activities involving healthcare providers will comprise Time 3. Midwives will be approached to complete an emailed or paper-based survey (as per respondent preference) in the final six months of the data collection period for each model of care. Semi-structured key informant interviews with other healthcare professionals will also be conducted during this time. These data will be used to address the study’s clinical- and cost-effectiveness outcomes, as well as health care provider perceptions of the acceptability and perceived benefit of each model of care. Additional administrative and clinical data will be collected during periods of observation by the Research Officer throughout the allocation periods for each model of care, and focus groups will be held approximately 3 months after the introduction of the PIPA model.

### Consent processes for women attending the participating site

Permission to waive patient consent for the collection of Time 1 data has been granted by the governing Human Research Ethics Committee. For Time 2, women who express an interest in participating in this component of the study (indicated to the midwife at the time of the initial psychosocial assessment) will be subsequently contacted by research staff. At this time, women who agree to take part will give their informed consent.

### Participant eligibility and expected sample sizes

The estimated sample sizes for Time 1 and Time 2 is predicated on the number of births at the participating site (approximately 4000 women per annum), the proportion of these women who complete the initial psychosocial assessment (approx. 85%) and expected rates of participation at Time 2 (approx. 15-20% of all English-speaking women attending the site for their booking in visit).

*Time 1:* De-identified information relating to all women who attend the study site for their antenatal care will be included in the study database for Time 1, with an estimated total sample size of 7000 women completing a routine psychosocial assessment during the data collection periods for each model of care (3500 women per SAFE START and PIPA models of care).

*Time 2:* Only women who, at Time 1, respond ‘yes’ to an expression of interest (EoI) to be involved at Time 2 will be contacted by the Research Officer. Women who have not completed the routine psychosocial assessment during pregnancy, who are clients of the hospital’s Indigenous Midwifery service (due to differences in the models of care and service delivery) and/or who are unable to complete the Time 2 questionnaires in English will not be contacted to take part in Time 2. The anticipated total sample size for Time 2 is 1300 women (650 per model of care).

*Time 3:* Study participants will include up to 40 healthcare providers who are responsible for conducting the psychosocial assessment or providing emotional and mental health care for women who attend the participating site for antenatal care (representatives from psychiatry, social work, mental health nursing, midwifery, administration, hospital data management). All relevant staff will be invited to contribute data to Time 3 (via one or more of survey data, observational data, key informant interviews; focus groups); however, staff that provided care under only one of the models (i.e., SAFE START or PIPA) will be ineligible for focus group participation. The numbers of health care professionals anticipated to contribute data for each mode of data collection are: survey data (est. *n* = 25), observational data (est. *n* = 5–10), key informant interviews (est. *n* = 5–10) and focus groups (est. *n* = 8–16 individuals).

To enable economic assessments to be completed, data relating to time spent by midwives at booking, time spent by administrative staff collecting and distributing files for new bookings (approx. est. *n* = 30 files per staff member) will be recorded under both models of care. Data on the time spent discussing referrals to the social work department (*n* = 120), the mental health midwife (*n* = 120) and weekly MCD (*n* = 50) will also be recorded for each model of care. Information relating to the clinical ‘correctness’ of these referrals will also be collected: this will be determined by the consensus opinion of key senior clinicians at the weekly MCD (perinatal psychiatrist, mental health midwife, senior midwife, and senior social worker) or the weekly file review (‘triage’) meeting of the mental health midwife and senior social worker.

### Data sources, measures and procedures

#### Time 1: Initial psychosocial assessment conducted at the antenatal ‘booking in’ visit

The hospital data management system (ObstetriX and subsequently eMaternity) will be used to identify all women who attended the participating site during the data collection periods for the PIPA Project, and for whom a routine psychosocial assessment was completed. The Time 1 dataset will include: date of booking in visit and psychosocial assessment; gestation and maternal age at this time; maternal date of birth; estimated date of delivery; partner status; gravidity (including reason for pregnancy loss, where available); parity; country of birth; physical health conditions; type of conception; model of maternity care; EPDS: total and Q10 scores; EPDS: item level responses (SAFE START only); psychosocial questions: item level responses; psychosocial questions: total score (PIPA only); referral/s indicated as a result of the psychosocial assessment (yes/no); referral/s indicated as a result of the psychosocial assessment (specified; PIPA only); language; interpreter needed; financial class (public, private or overseas patient); and Time 2 Expression of Interest response (yes/no). Time 1 data will be extracted by the data manager at the participating site at approximately weekly intervals, for all women allocated to the SAFE START and PIPA models of care.

#### Time 2: Two weeks post-time 1

Women who consent to participation at Time 2 will complete the EPDS [6], the ‘Whooley’ questions [19] followed by a third ‘help’ question [20], the Generalized Anxiety Disorder Scale [GAD-7] [21], the Matthey Generic Mood Questionnaire (MGMQ) [22], an ‘interval’ question to assess perceived change in emotional wellbeing at Time 2 [27] and the Mini International Neuropsychiatric Interview v6.0 [M.I.N.I.; mood and anxiety disorder modules only] [23]. Women will also complete a short survey covering the acceptability of the psychosocial questions and assessment process.

‘Key Survey’™ will be used as the platform for data collection for all Time 2 measures *except* the M.I.N.I., which will be collected using infrastructure provided by Medical Outcomes Systems (to whom the online M.I.N.I. is copyrighted). Alternatively, these questionnaires will be administered by phone by the Research Officer verbatim, with participant responses captured in the project-specific ‘Key Survey’ and MINI instruments.

#### Time 3: various data collection points during the model of care allocation periods

*Survey for health professionals:* Study-specific survey questions will address a range of issues related to the experience of healthcare professionals (in particular, midwives) in providing psychosocial care to women during pregnancy, including: level of comfort in asking the psychosocial questions; level of confidence in discussing responses to the psychosocial assessment and (if required) referral and support options; time spent administering the initial psychosocial assessment; time spent initiating any referrals; ease of use of computer-based assessment tool; and utility of referral advice and the psychosocial summary report (listing key issues and referral prompts arising from the psychosocial assessment), for each model of care. ‘Key Survey’™ will be used as the platform for data collection for the healthcare professional feedback questionnaire. Paper versions of the questionnaires will be provided to healthcare professionals who do not have internet access, or who would prefer to complete the measures in hardcopy.

*Observational data and key informant interviews:* The following information will be collected for each model of care: time spent by clinical and administrative staff on administrative tasks directly related to psychosocial care, including collecting and distributing files for new bookings where a psychosocial referral was made; time spent ‘triaging’ and allocating these files as appropriate; time spent on case discussion at the MCD for new bookings; and other relevant administrative tasks.

As part of the Time 3 data collection, the Research Officer will also attend the weekly psychosocial ‘triage’ and MCD meetings to collate referral pathway data for women in each model of care. This will include information on the number and proportion of women for whom a referral was made from their initial psychosocial assessment, and the number and proportion of women considered ‘correct’ and ‘incorrect’ referrals. The Research Officer, in consultation with the relevant on-site departments and clinicians, will collate this information for both models of care. This process will also be facilitated by the Research Officer observing/shadowing the day-day activities of key staff.

*Focus groups:* Health care professionals providing psychosocial care for pregnant women at the study site will be invited to participate in a study-specific focus group. These may include midwives, social workers, mental health midwives and psychiatrists. The focus groups will explore participants’ experiences of providing the alternative models of psychosocial care, including (but not limited to) time and ease of administration, understanding of risk levels (including nomenclature) and perception of care quality for the woman. A question guide will be used to facilitate discussion and will be informed by key themes from existing literature, consultation with experts and feedback captured in the Time 3 surveys. Each focus group will be approximately 60–90 min in duration. Discussion will be recorded with the permission of participants using digital audio recorders and will be transcribed verbatim.

#### Resource consumption and unit resource cost estimates

The economic evaluations will be informed by survey data, observational data, key informant interviews and focus groups during the trial period and will be completed at Time 3. Bottom up costing methods based on the principle of opportunity costs forgone will be employed to capture the direct costs of identifying ‘correct’ and ‘incorrect’ referrals cases. The Research Officer will time each activity associated with completing psychosocial assessment and administrative tasks associated with the initiation of referrals to various site-based support services (see Box). This will allow the allocation of costs for each activity for inclusion in the cost-effectiveness analysis. The salary costs applied for each unit of activity will be taken from NSW Health Service Awards. Overhead costs will not be applied because they are equivalent between the two models of care. Because the PIPA Project has been designed to primarily inform decision making around effectiveness, efficiency and acceptability of a psychosocial screening program from the perspective of the maternity sectors, indirect patient costs associated with travel etc will not be included, nor will the costs associated with downstream, clinical care or interventions and the broader burden associate with mental illness. Costs will be presented in constant Australian dollars (AUD) (Table 2).

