^b^‘Complex’ risk factors : homelessness or housing instability; domestic violence; substance misuse; contact with child protection services

^c^‘Social’ risk factors: young maternal age (less than 20 years); no partner; booking-in appointment at >20 weeks gestation

**Table 2 Tab2:** Data collection schedule and measures

Measure	Time 1 *All women (routinely collected data)*	Time 2 *Consenting women only*	Time 3 *Health professionals only*
Demographic information^a^	X		
EPDS^a^	X	X	
Psychosocial assessment^a^	X		
Routine referral information^b,c^	X		
Feedback survey (women)^d^		X	
Costing data	X		X
Feedback survey; observational data; key informant interviews; focus groups (health professionals)^b,c,e^			X
Whooley questions^f^		X	
GAD-2^f,g^		X	
MGMQ^f,g^		X	
MINI^f,g^		X	
Interval question^f,g^		X	
Brief help seeking items^f,g^		X	

*EPDS* Edinburgh Perinatal Depression Scale, *GAD-2* Generalized Anxiety Disorder Scale-2items, *MGMQ* Matthey Generic Mood Questionnaire, *MINI* Mini International Neuropsychiatric Interview (v6.0; mood and anxiety disorder modules only; Data will be used to address: ^a^All aims; ^b^Primary Aim 1 (clinical effectiveness); ^c^Primary Aim 2 (cost effectiveness); ^d^Primary Aim 3 (pregnant women perspectives); ^e^Primary Aim 3 (health care provider perspectives); ^f^Secondary Aim (psychometric evaluation). ^g^Completed by women allocated to the PIPA model of care only

*Primary Aim 2: Cost-effectiveness outcomes:* To quantify: i) the cost per ‘correct’ and ‘incorrect’ referral made at the initial psychosocial assessment, for each model of care; ii) the incremental cost per ‘correct’ referral made and the incremental cost per ‘incorrect’ referral averted by the PIPA model compared to the SAFE START model; and, iii) the budgetary implications of implementing the PIPA model at the participating site, based on number of women assessed.

*Primary Aim 3: Consumer perspectives:* To compare the acceptability and perceived benefit of each model of care from the perspective of both pregnant women and their healthcare providers.

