#### Cost-effectiveness analysis

The primary outcome variable for the cost-effectiveness analysis (Primary Aim 2) will be the proportion of ‘correct’ referrals initiated and ‘incorrect’ referrals averted. The incremental costs and effects of SAFE START compared to PIPA will be expressed as the incremental cost-effectiveness ratio (ICER). The ICER combines the net changes in effects with the net change in costs between two strategies providing a relative estimate of the cost-effectiveness of the PIPA program relative to the SAFE START program. The ICER per ‘correct’ referral made and per ‘incorrect’ referral averted will be estimated using mean costs and effects and represented with 95% confidence intervals for the ICERs using non-parametric bootstrapping techniques. One-way and multivariate probability sensitivity analysis using Monte Carlo simulations across the cost and effect distributions will be undertaken to investigate uncertainty around the ICERs. Based on number of women screened and proportion of ‘correct’ and ‘incorrect’ referrals identified, the economic evaluation will allow a budget impact analysis to be undertaken to determine the costs of running SAFE START and PIPA at other maternity hospitals.

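### Dropping overheads as equivalent is justified only for the incremental results, and the costing as described does not reach the PIPA-only staff training

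*Protocol article*

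**What the plan says.** All references are to the protocol article.

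- **Scope of costing** (Resource consumption and unit resource cost estimates). Costing is bottom-up and meant to "capture the direct costs of identifying ‘correct’ and ‘incorrect’ referrals cases". The activities are described thus: "The Research Officer will time each activity associated with completing psychosocial assessment and administrative tasks associated with the initiation of referrals", with a pointer to a Box that is not in the text at hand. Prices are salaries: "The salary costs applied for each unit of activity will be taken from NSW Health Service Awards".
- **Overheads** (same section). "Overhead costs will not be applied because they are equivalent between the two models of care". Patient travel, downstream care and the wider burden of mental illness are also excluded by name. Training and set-up are not mentioned either way.
- **What is to be estimated** (Aims, Primary Aim 2). (i) The cost per correct and per incorrect referral in each model; (ii) the incremental cost per correct referral made and per incorrect referral averted; (iii) "the budgetary implications of implementing the PIPA model at the participating site, based on number of women assessed".
- **Budget analysis** (Cost-effectiveness analysis). It starts "Based on number of women screened and proportion of" correct and incorrect referrals, and its stated product is what it costs to run each model at other maternity hospitals.
- **Resources only PIPA uses.** Setting refers to "one month of staff training for the PIPA model". The Fig. 2 legend puts this in the last month of Year 2, a year without data collection. The description of the PIPA model adds a decision algorithm and referral prompts inside eMaternity.

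**The concern.** A cost that is the same in both models cancels when one model is subtracted from the other. It does not cancel in an average cost for one model, or in one model's total. The plan gives a single reason for leaving overheads out of everything, yet two of its outputs are not differences.

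The training question is separate. Training is staff time that only PIPA requires, and the plan values resources by opportunity cost, under which those hours count. If they are never recorded, they are missing from the one output that is explicitly about implementing PIPA, and the omission runs in PIPA's favour. A hospital using the results to decide on adoption would see a budget without part of its start-up cost.

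**Working it through.** The plan states no cost, overhead rate, training hours, ICER or budget, so there is no figure of its own to reproduce. The check is algebra followed by an illustration.

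**Notation.** c = direct cost per woman; e = correct referrals per woman assessed; subscripts S (SAFE START) and P (PIPA); H = overhead per woman; r = overhead as a share of staff cost; T = one-off PIPA-only cost; N = 3,500 women per model (Participant eligibility and expected sample sizes).

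**Formulas.** Average cost per correct referral = c/e. ICER = (cP − cS)/(eP − eS).

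- Equal H per woman: each average rises by H/e; the ICER is unchanged; each model's running cost rises by N × H; the difference in budget for the same number of women is unchanged.
- Overhead proportional to staff cost: averages and ICER are all multiplied by (1 + r), so nothing cancels.
- PIPA-only T: PIPA's average rises by (T/N)/eP, the ICER by (T/N)/(eP − eS), and the site budget by T.

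**Illustration (every cost and yield is an assumption).** cS = 40, cP = 42 (A$); eS = 0.20, eP = 0.25.

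- Base: 40/0.20 = 200; 42/0.25 = 168; ICER = 2/0.05 = 40.
- H = 5: 45/0.20 = 225; 47/0.25 = 188; ICER still 40. H = 20: 60/0.20 = 300; 62/0.25 = 248; ICER still 40. The gap between the two averages grows from 32 to 37 and then 52. Running cost per model rises by 3,500 × 5 = 17,500 to 3,500 × 20 = 70,000.
- Proportional, r = 10%: averages 220 and 184.8, ICER 44. r = 50%: 300 and 252, ICER 60.
- Training only, at an assumed A$50 per hour. The staff counts 25 and 40 are borrowed from the Time 3 estimates and the hours are assumed. 25 × 2 × 50 = 2,500, or 0.71 per woman: PIPA average 170.86, ICER 54.29. 40 × 8 × 50 = 16,000, or 4.57 per woman: PIPA average 186.29, ICER 131.43.
- If PIPA is instead assumed to save money (cP = 36, base ICER −4/0.05 = −80), the same training range moves the ICER to between −65.71 and +11.43.
- PIPA-specific configuration, the least supported input: an assumed 20,000 to 50,000 adds 5.71 to 14.29 per woman (20,000/3,500 and 50,000/3,500).

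Charging T to one year's women gives the largest per-woman effect; annualising over several years shrinks it.

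**Would the described data collection pick up training?** The timed items are booking, file handling, triage, referral discussion, case discussion meetings and related administration (Participant eligibility and expected sample sizes; Time 3). Time 3 collection is tied to the periods when each model is in use (Time points for data collection). Training happens before the PIPA period, in an interval for which Setting and the Fig. 2 legend both say no study data are collected. Followed literally, the text would not capture it.

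**The case against.** The case for the plan has real force.

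- **A direct-cost scope is declared.** Overheads that do not depend on the model are not forgone, so leaving them out is coherent for a comparison. The between-model efficiency measure is the incremental ratio, which equal overheads do not touch. This stands: per-model figures are correct as direct costs and understated only if read as full costs. What remains is that the plan does not say how Aim 2(i) and running-cost figures are to be read, and the reason it gives does not cover them.
- **Training is not excluded.** The Box is not shown, the article condenses a fuller protocol, and interviews, surveys and other administrative tasks also feed the costing. This stands as to proof. It is weakened because the sentence introducing the Box concerns assessment and referral-initiation activities, and because of when training takes place.
- **eMaternity is a state-wide replacement.** This stands. Only configuration specific to PIPA could be incremental, and the article does not say who pays for it.

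A reader might infer that the overhead rule invalidates the ICER or the cost of moving to PIPA. The documents do not support that: with equal overhead per woman, both are unchanged. The ICER is affected only if overhead follows staff time. That is possible, since PIPA scores automatically and narrows the threshold for case discussion meetings (Table 1; Key differences between the models), but it is not shown.

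**Conclusion.** The point holds in limited form and merits a change.

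1. Equivalence justifies omitting overheads from the ICER and the incremental budget, provided overhead is equal per woman. It does not justify omitting them from per-model cost per referral or per-model running cost. As full costs, the averages are understated by H/e, an amount that differs between models whenever referral yield differs.
2. The costing as described does not reach PIPA-only training. If the Box does not add it, the site budget for implementing PIPA is understated by T, and the ICER looks better for PIPA than one that charges training (taking PIPA to yield more correct referrals). This is likely, not proven.

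The size is unknown. The illustration shows only that a small sum per woman is magnified when divided by a small difference in yield: at an assumed difference of 0.05, each A$1 per woman moves the ICER by A$20. It would be too strong to conclude that the cost results will be wrong, or that the whole eMaternity build is a missing PIPA cost. The documents support neither.

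**What to change.** - Restrict the equivalence statement to the incremental results, and state that it assumes equal overhead per woman.
- Label the Aim 2(i) and running-cost figures as direct costs, and add a sensitivity analysis with a standard overhead rate.
- Record PIPA training hours and value them at award rates. Add any PIPA-specific eMaternity configuration borne by the maternity sector, but not the state-wide platform. Enter both as one-off costs in the site budget impact, and annualise them over a stated life in an ICER sensitivity analysis.
- Reconcile Aim 2(iii), which concerns implementing PIPA at the participating site, with the analysis section, which concerns running both models at other hospitals.

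The cost is a few extra inputs from hospital records and extra rows in the model. Study status says PIPA data collection had yet to start, so the hours should still be recordable or recoverable. The downside is that PIPA may look slightly less favourable in its first year.
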